**INTERVENTION**

The TDF is manufactured as tablet and will be taken orally. The dose will be 300mg/day.

The therapy will be performed in three hospitals of China (The First Affiliated Hospital of Medical College of Xi’an Jiaotong University, Shaanxi Provincial People Hospital and Maternal and Child Health Care Hospital of Xinjiang Uygur Autonomous Region). The study will last for 4 years from January 2013 to December 2016.

The TDF therapy will be started at 24 weeks of gestation. To evaluate the effect of TDF, the blood sample will be collected in all the pregnancies with/without TDF treatment before initiating the TDF therapy, then every 4 weeks till just before delivery. After delivery, this procedure continues till 28 weeks postpartum. After collecting the blood, the parameters related to live function and HBV infection will be checked within 24h. The aliquot of blood will be used to extract DNA using DNAout kit to check the expression of HBxAg and the mutation of drug resistant genes. The left will be used to harvest serum. In brief, the blood will be kept in ice for 30min before the centrifugation. The serum will be aliquoted and kept at 80°C for the further analysis. All sample tubes will be labelled with the case number of patient.

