① co-infection with HIV, HCV or HDV; ② HBV treatment history within 6 months; ➂ abortion history or clinical manifestation of inevitable abortion; ④ congenital deformity of foetus; ⑤ hepatocellular carcinoma evidence, renal or hepatic dysfunction, creatinine clearance rate <100mL/min, alanine aminotransferase (ALT) >5 times of upper limit of the normal level, bilirubin >2mg/dl; ⑥haemoglobin <8g/100mL, neutrophil <1000/mm^3^, albumin <2.5g/100mL; ⑥ special medicine treatment during the pregnancy; ⑦ biological father of infant has chronic HBV infection.

- Randomization

Based on our prediction, less than 50 pregnancies per year are eligible for the study. To ensure the similar number for treatment and control group, we estimate that minimal 30 subjects can participate in the study (total around 120 subjects). When getting 120 subjects, the enrolment will be stopped.

In random number table, we randomly start and separate 3 digital number as group following the order in number table. The separated number are written on the paper following the order of the random number table. The repeated number and number big than 120 will be excluded. The first 60 number based on the order will be allocated as TDF treatment. The left will be controls.

- Conceal the intervention

The selected number and corresponding intervention will be hided in the individual envelope and sealed. On the surface of the envelop, the selected number is written. Then the envelops are managed in order (from 001 to 120) and given to the doctor when having the enrolled subject (visiting order).

- Ethics

We have got the approval from the hospital for the study (approval N° 2012-136). The consent will be prepared and printed. The patients will be informed and sign the written consent.

- Potential benefit to the subjects

The TDF therapy in the HBV-infected pregnant women with high viral loads will help in reducing the risk of mother-to-child transmission. It will also protect mothers during the gestation periods due to the special immune situation. In addition, it will help to understand the safety and efficacy of TDF in blocking the vertical transmission, its effect on mothers and infants and potential adverse effects, which will facilitate the TDF treatment in the pregnancies in clinic.

- Potential risk

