The most potential risk for the trial is the side effects of TDF, such as preterm delivery and severe adverse effects including dysfunction of liver and kidney as well as the HBV resistance to TDF treatment. The trial has no apparent physical, psychological and economic effect. The pregnancies will not have any stress or discomfort when answering the question or focusing on the research. The participants will face the same stress as other pregnancies when collecting blood routinely.

- Methods to protect the privacy, data and right of subjects

Before starting the trial, the participants will be informed, agree and sign the printed consent. All the personal information will be confidential. A person will specifically manage the collected data that will be saved in the computer with password. Only this person can access the computer.

- Intervention

The TDF therapy will be given to the pregnant women who are HBsAg/HBeAg-positive with high viral burdens. The details of the medicine will be concealed. The pregnancies will take the medicine orally, 300mg/day, starting the date of enrolment (24 weeks of gestation) until 4 weeks postpartum. This dose is recommended by the manufacture and also used by most of the studies. The method used for assigning subjects to the treatment group is described above in the section of randomization.

The medicine will be distributed to the participants every time when visiting the doctor. The medicine will be prepared and packaged in the pharmacy centre of the hospitals.

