**STUDY PROCEDURES**

- Screening for eligibility

The participants will be screened by the consulting doctor when they visit the hospital for the first time based on the criteria. The potential eligible pregnancies will be monitored every 4 weeks till 24 weeks of gestation. According to the parameters of pregnancies at 24 weeks of gestation, the pregnant women will be enrolled or not for the study.

- Visit

The enrolled pregnant women will visit the doctor every 4 weeks till 28 weeks postpartum.

- Data collection

Routinely, when patients visit doctor for the first time, all personal information will be recorded as electronic file including birth date, home address, contact information, family condition (family members, estimated annual income, work condition, etc), health history, etc. The medical records from other hospital(s) will also be collected.

The consulting doctor will provide the prescription for the lab examination or other examination such as ultrasound and infant monitor. All the obtained results from the examination will send back to the doctor. The person who is charge of the study will record all data in the specialized computer.

- Outcomes measurement

The primary outcome is the mother-to-child transmission of HBV infection, which will be determined when the infant’s serum HBV DNA is higher than 20 IU/ml or HBsAg is positive 28 weeks after the birth.

The secondary outcome is the recovery of HBV DNA levels at 28 weeks postpartum in the pregnancies with or without TDF treatment after the cessation of TDF treatment.

- Safety and adverse event monitoring

The doctor will carefully ask the condition and situation of the pregnancies during the consultation. At the same time, the safety is also monitored by the blood assay.

Based on the severity of patients’ situation (vomit, rash on the skin, liver and kidney function, etc), the doctor will give the corresponding treatment and decide whether withdrawing the study for the patient.

The emergence contact information will be provided to the pregnancies in case needing help and suggestion from doctor as well as reporting the adverse events. All the adverse effect will be recorded till the complement of the follow-up.

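### The protocol promises concealment of the medicine without saying from whom or how, and no procedure supports masking after enrolment, so the doctor-elicited symptom comparison is open to ascertainment bias

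*Protocol*

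**What the plan says.** **The concealment statement.** The Intervention item under Study Design says "The details of the medicine will be concealed". It stands between the description of who receives TDF and the description of how it is taken. No person from whom the details are hidden, and no means of hiding them, is given.

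**Allocation.** The item headed Conceal the intervention, also under Study Design, says "The selected number and corresponding intervention will be hided in the individual envelope and sealed". The envelopes are then "given to the doctor when having the enrolled subject (visiting order").

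**The control condition.** The Intervention section says "the blood sample will be collected in all the pregnancies with/without TDF treatment". The secondary outcome under Study Procedures is likewise assessed "in the pregnancies with or without TDF treatment after the cessation of TDF treatment". The protocol mentions no placebo or dummy tablet, and does not use the terms blind, mask or open-label.

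**Distribution and results.** On supply, the Study Design item says "The medicine will be distributed to the participants every time when visiting the doctor". Packaging is done in the hospitals' pharmacy centre, and the person who hands the drug over is not named. The Intervention section has HBV and liver parameters checked every 4 weeks until delivery and continues sampling afterwards. The Data collection item under Study Procedures returns examination results to the doctor.

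**Safety.** Under Safety and adverse event monitoring, "The doctor will carefully ask the condition and situation of the pregnancies during the consultation". The doctor then acts on the severity of problems such as vomiting, rash, and liver or kidney dysfunction, and decides on withdrawal. The Statistical Analysis section compares safety outcomes between the arms by t-test, chi-square test or Fisher's exact test.

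**The concern.** A statement that the medicine is concealed leads a reader to expect that women, doctors or both do not know the arm during follow-up. If nothing delivers that, symptoms are asked about and judged by someone likely to know the assignment, and reported by women likely to know whether they are on TDF. A difference produced by asking or reporting could then be taken for a drug effect, and a balanced result could be trusted more than it deserves.

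This matters because clarifying the adverse effects of TDF is one of the five stated study objectives. There is also a less direct route to the efficacy analysis. Study Design excludes women after enrolment for severe side effects, and the doctor decides on withdrawal. A judgement made with knowledge of the arm could therefore influence who contributes an infant outcome.

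**Working it through.** The protocol gives no figure for this point, so the main check is to set its passages side by side. A numerical illustration follows.

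**1. Does any procedure support masking after enrolment?**

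| Route to knowing the arm | What the protocol provides |
|---|---|
| Assignment | The envelope contains the intervention and is given to the doctor at enrolment. It protects the allocation only until it is opened. |
| Treatment received | TDF against without TDF. No placebo, matching tablet or coded packaging is described. |
| Laboratory results | HBV parameters every 4 weeks, with results returned to the doctor. |

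The third route would probably reveal the arm even if a placebo existed. The Introduction cites an 8-woman series in which HBV DNA fell by 2-4 log10 copies/mL in the first 4 weeks on TDF. A fall of that order in women who enter at 6.3 log10 IU/mL or above would be plain to a doctor who sees the results.

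**2. Does the knowledge reach an outcome that is open to judgement?** The doctor asks about symptoms, and no fixed list of questions is given. The doctor also judges severity and decides on withdrawal. Safety outcomes are then tested between arms. The primary outcome (infant HBV DNA or HBsAg at 28 weeks) and the secondary outcome (maternal HBV DNA at 28 weeks postpartum) are laboratory measures, so questioning and reporting do not touch them directly.

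**3. How large could the effect on symptoms be?**

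Input from the protocol: 60 women per arm (Randomization: the first 60 of 120 numbers go to TDF, the rest to control). Assumptions not in the protocol: the same true symptom rate in both arms (20% or 30%), full recording on TDF, and recording of 100%, 80%, 60% or 40% of control events.

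Formula: expected recorded rate = true rate × fraction recorded.

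At a true rate of 20%:
- 80% recorded in controls: 0.20 × 1.0 = 0.20 v 0.20 × 0.8 = 0.16; difference 0.04, risk ratio 0.20/0.16 = 1.25.
- 60% recorded in controls: 0.20 v 0.20 × 0.6 = 0.12; difference 0.08, risk ratio 0.20/0.12 = 1.67. In women, that is 60 × 0.20 = 12 v 60 × 0.12 = 7.2.

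Chance that a two-sided Fisher test at 0.05 is significant when TDF has no effect on symptoms, summed over the two binomial distributions with 60 per arm:

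| Control events recorded | True rate 20% | True rate 30% |
|---|---|---|
| 100% | 2.8% | 3.1% |
| 80% | 5.4% | 7.8% |
| 60% | 15.3% | 26.1% |
| 40% | 37.7% | 60.5% |

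With mild under-recording the error rate stays near the nominal 5%. With marked under-recording it does not. The protocol gives no basis for choosing among the rows.

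**The case against.** The strongest reply is that no masking is claimed. The document describes itself as a translation of the key points of a Chinese protocol, never calls the trial blinded, and elsewhere uses the word conceal only for the sealed envelopes. The sentence may loosely restate the envelope procedure. That reading is possible, and it is why the sentence is better called ambiguous and unsupported than false. It does not remove the point. Envelope concealment has its own heading, the sentence describes the medicine, and the same paragraph separately refers back to the randomization section for the method of assignment. If only the envelopes were meant, the same rewording resolves it.

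Three limits on the concern also stand:
- The efficacy outcomes are laboratory measures.
- The Statistical Analysis section does not list the safety outcomes. That symptoms such as vomiting and rash are among those tested is the probable reading, but it is not stated.
- The figures above rest on assumed rates, and differential ascertainment is a feature of any open-label trial.

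A reader might infer more than the text supports:
- *That controls are said to receive no tablets.* This is a reasonable inference from the wording on treatment with or without TDF and the absence of a placebo, but the protocol does not state it.
- *That the consulting doctor opens the envelope and hands out TDF.* The envelope is given to the doctor. Who opens it, who dispenses, and whether the same doctor takes the adverse event history are not stated, although one doctor for both envelope and history is the natural reading.
- *That concealment conflicts with informed consent.* It does not, because masked trials also inform participants before they sign.
- *That assay staff are left unmasked because masking is assumed to be in place.* No reason is given. Tubes are already labelled by case number, and only a statement on access to the allocation list is absent.

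**Conclusion.** The point holds in a limited form. The concealment sentence has no procedure behind it, and the procedures that are described point to treatment being known after enrolment. Alongside this, symptoms are elicited by open questioning from the doctor, who also judges severity and withdrawal, and safety outcomes are compared between arms by significance test. The symptom comparison is therefore open to ascertainment bias.

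The size of the bias is unknown. Under the assumptions shown, the false-difference rate runs from 5.4% to 37.7% at a true rate of 20%, and from 7.8% to 60.5% at 30%, as recording of control events falls from 80% to 40%. These figures show sensitivity and are not estimates for this trial.

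The primary and secondary outcomes are much less exposed. Their remaining exposure runs through withdrawal and exclusion decisions rather than through measurement. It would go too far to say that the trial's masking has failed, because the document does not clearly claim any.

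**What to change.** 1. Replace the concealment sentence with a statement that allocation is concealed by sealed envelope until enrolment and that treatment is open-label thereafter. If a masking procedure does exist, state instead who is masked and how.
2. Use the same fixed symptom checklist at every visit in both arms.
3. Require staff who run the infant HBsAg and HBV DNA assays and the maternal safety assays to work from the existing case-number labels, without access to the allocation list.
4. Report elicited symptoms as open-label data.

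The cost is a change of wording and a short form at each visit. Visits are already on the same 4-weekly schedule in both arms and tubes already carry case numbers, so no new infrastructure is needed. The downside is a weaker claim from the symptom data. No dose, schedule or clinical rule changes.

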**STUDY PROCEDURES**

- Screening for eligibility

The participants will be screened by the consulting doctor when they visit the hospital for the first time based on the criteria. The potential eligible pregnancies will be monitored every 4 weeks till 24 weeks of gestation. According to the parameters of pregnancies at 24 weeks of gestation, the pregnant women will be enrolled or not for the study.

- Visit

The enrolled pregnant women will visit the doctor every 4 weeks till 28 weeks postpartum.

- Data collection

Routinely, when patients visit doctor for the first time, all personal information will be recorded as electronic file including birth date, home address, contact information, family condition (family members, estimated annual income, work condition, etc), health history, etc. The medical records from other hospital(s) will also be collected.

The consulting doctor will provide the prescription for the lab examination or other examination such as ultrasound and infant monitor. All the obtained results from the examination will send back to the doctor. The person who is charge of the study will record all data in the specialized computer.

- Outcomes measurement

The primary outcome is the mother-to-child transmission of HBV infection, which will be determined when the infant’s serum HBV DNA is higher than 20 IU/ml or HBsAg is positive 28 weeks after the birth.

The secondary outcome is the recovery of HBV DNA levels at 28 weeks postpartum in the pregnancies with or without TDF treatment after the cessation of TDF treatment.

- Safety and adverse event monitoring

The doctor will carefully ask the condition and situation of the pregnancies during the consultation. At the same time, the safety is also monitored by the blood assay.

Based on the severity of patients’ situation (vomit, rash on the skin, liver and kidney function, etc), the doctor will give the corresponding treatment and decide whether withdrawing the study for the patient.

The emergence contact information will be provided to the pregnancies in case needing help and suggestion from doctor as well as reporting the adverse events. All the adverse effect will be recorded till the complement of the follow-up.

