**Abstract*:**

After more than 20 years of studies on the mother-to-child transmission and the therapy strategies against hepatitis B virus (HBV) infection, we have known that the HBsAg/HBeAg and HBV DNA level are the predominant factors related to the HBV intrauterine infection. The present project will prospectively investigate the effect of tenofovir disoproxil fumarate (TDF), a nucleotide analogue against viral infection, in blocking the HBV vertical transmission and the potential mechanism involved in this process among the pregnant women who are HBsAg/HBeAg-positive with high viral loads. The trial will be randomly designed. We will check the efficacy and rationality of the TDF in blocking the mother-to-child transmission of HBV infection (primary outcome). We will dynamically monitor the HBsAg/HBeAg, HBV DNA levels (secondary outcome) and liver function of the women during the pregnancy and the hepatitis B parameters, HBV DNA level (secondary outcome) and liver function of infants immediately after the birth and at age of 7 months. The ratio of T lymphocytes and cytokines level in the serum related to the HBV infection will also be checked (before TDF intervention, before and after delivery, etc) to reveal the effect of TDF on the immune function of the pregnancies, which will help to determine whether the changes of immune system by TDF contribute to the block of vertical transmission of HBV. The known and/or potential mutation site(s) of genes related to the drug resistance or tolerance will be examine by PCR in the pregnancies after TDF treatment, which will facilitate the subsequent therapy against chronic HBV infection. The infants from TDF treated mothers will be followed up till 2 years old and monitor the growth curve and IQ value. In summary, the present study will allow us to evaluate the efficacy and safety of TDF in the pregnancies and to provide the evidence of TDF against HBV during the pregnancy.

*** Since the original protocol was wrote in Chinese and there are too much contents, I try my best to translate the key points of the protocol into English.**

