**STUDY OBJECTIVES**

The present prospective study aims at investigating the effect of TDF against the mother-to-child transmission of HBV infection. Through this trial, we will:

(1) confirm the efficacy of TDF in blocking HBV intrauterine infection during pregnancy;

(2) monitor the effect of TDF on the dynamic changes of HBV DNA levels in the pregnancy;

(3) test the HBsAg and HBeAg expression during and after the TDF treatment;

(4) screen the changes of HBV resistance genes related to the NAs treatment in the pregnant women with chronic HBV infection;

(5) clarify the adverse effects induced by TDF treatment during the pregnancy for both mother and infants.

This clinical project will allow us to better understand the safety and efficacy of TDF against HBV infection during the pregnancy. It will also help in clarifying the potential adverse effects of this medicine. The study will also provide the evidence to further optimize and to facilitate the TDF application in blocking the vertical transmission of HBV infection.

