**STATISITICAL ANALYSIS**

- All data will be collected together to the person who is in charge of data collection. The data will be save as Excel file format.
- When the study is finished, we will discuss with statistician from the host university in managing and analyze the data.
- The data will be presented as mean±SE and SPSS18.0 (SPSS inc., Chicago, USA) will be used for the analysis. Baseline characteristics and safety outcomes will be compared between the TDF treatment and the controls using t-tests for continuous variables and chi-square tests or fisher exact tests for categorical variables. The Mother-to-child transmission rate and the recovery levels of the HBV DNA 28 weeks after the delivery between the two groups will be compared by Fisher exact tests. A mixed model, repeated measures analysis for variance will be used to analyze if the serum HBV DNA levels change differently with or without TDF treatment. The planned contrasts will be tested for the "change in HBV DNA for each group between baseline and delivery time" and "differences from weeks to the weeks’ within TDF treatment group. The p value less than 0.05 will be considered as statistically significant.
- All data will be confidential during and after the study. The data will be transferred and stored in the server of the hospital. Special authorization is needed to access these data after the closure of the study.

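### Infant harms are part of objective 5, but the only infant safety measure specified for both arms is liver function at birth and 7 months

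*Protocol*

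**What the plan says.** Item 5 of the Study Objectives is to "clarify the adverse effects induced by TDF treatment during the pregnancy for both mother and infants".

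Under Study Procedures, the text on safety and adverse event monitoring begins: "The doctor will carefully ask the condition and situation of the pregnancies during the consultation". It adds monitoring by blood tests. The protocol uses the word 'pregnancies' for the pregnant women; in its Intervention text, they are the ones who take the tablets. The doctor's decisions are tied to signs in the patient: "Based on the severity of patients’ situation (vomit, rash on the skin, liver and kidney function, etc". The section ends: "All the adverse effect will be recorded till the complement of the follow-up". The visit schedule in the same chapter is for the enrolled women, every 4 weeks up to 28 weeks after delivery. The data collection text mentions examinations that a doctor may order: "lab examination or other examination such as ultrasound and infant monitor".

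Infant measurements are described mainly in the Abstract. With hepatitis B markers and HBV DNA it plans "liver function of infants immediately after the birth and at age of 7 months", without naming an arm. It then states: "The infants from TDF treated mothers will be followed up till 2 years old and monitor the growth curve and IQ value".

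The Potential risk text names preterm delivery among the side effects of TDF. Study Design lists preterm delivery as a ground for excluding a patient during the study. The Statistical Analysis section says: "Baseline characteristics and safety outcomes will be compared between the TDF treatment and the controls using t-tests for continuous variables". It does not list those outcomes.

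**The concern.** A safety objective can be answered only from data sought in the same way in both arms. Here the objective names the infant, while the questioning, the example signs and the visit schedule are about the mother. The infant is exposed in utero from 24 weeks of gestation to delivery, so birth is a natural point at which to look for harm. Yet birth weight, birth length, anomalies found at birth and later infant illness are not named as data to collect in either arm.

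The risk is a report that no infant safety signal was found when little was looked for. Events that reach the record only because a mother mentions them may be incomplete, and reporting may differ between arms.

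**Working it through.** The plan gives no figure for infant safety, so there is none to reproduce. Its sample size of 35 per group is built on transmission rates of 30% and 5% and plays no part here. The check sets the sections side by side.

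**What is planned for infants, and in which arm**

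| Item | Where stated | Arm | Use as a safety comparison |
|---|---|---|---|
| HBV markers and HBV DNA | Abstract; Outcomes measurement | Not limited to one arm | None: these measure efficacy |
| Liver function, birth and 7 months | Abstract | Not limited to one arm | Yes |
| Growth and IQ to 2 years | Abstract only | TDF only | None: no control infants |
| 'Infant monitor' | Data collection | Not stated | Not fixed: no content or timing |
| Preterm delivery | Potential risk; Study Design | Not limited to one arm | A reason for exclusion, not an outcome |
| All adverse effects | Safety monitoring | Not stated | Not systematic: does not say that infants are asked about |

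One row gives a specified infant safety measure in both arms.

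**Size of the gap**

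- Fetal exposure: the Intervention section starts TDF at 24 weeks of gestation. Assuming delivery at 40 weeks, 40 − 24 = 16 weeks. The protocol gives no delivery week, and each week earlier or later changes this by one.
- Postpartum contacts: visits every 4 weeks to 28 weeks give 28 / 4 = 7. The stated procedure does not mention asking about the infant at any of them.
- Infants: the randomization list has 120 numbers, the first 60 for TDF, leaving 120 − 60 = 60 controls.

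**What full collection could show, for context**

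With n = 60 infants in an arm and no event of a given kind, the one-sided 95% upper bound on its rate is 1 − 0.05^(1/60) = 0.049, or 4.9%. The chance of seeing at least one event is 1 − (1 − p)^60: 45.3% for p = 1%, 70.2% for p = 2% and 95.4% for p = 5%. These statements require that every infant is asked about or examined. Without systematic collection, a count of zero supports no such bound.

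**The case against.** Several stronger readings are tempting, and the document does not support them.

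- *Infants are examined only for HBV and liver function.* A reader might infer this from the birth and 7-month plan, but the Abstract also plans growth and IQ to 2 years. That follow-up lacks a control group and is absent from the visit, outcome and safety sections, but it exists.
- *There is no infant safety comparison at all.* Infant liver function is not limited to one arm, and the Statistical Analysis section does not confine safety outcomes to mothers. A comparison of liver function is therefore possible.
- *Infant events are never recorded.* The sentence on recording all adverse effects is not limited to the mother. It fixes how long recording lasts, however, and not who is asked.
- *Gestational age at delivery is not collected.* Applying the preterm exclusion requires it to be known. The defect is that it serves to exclude and is not named as an outcome.
- *Infant kidney tests are missing.* Potential risk names kidney dysfunction as a general TDF side effect. No infant kidney risk is stated and no infant sample volume is given, so an infant kidney assay would be a preference.

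Two general objections carry some weight. The Abstract says that only key points were translated from a longer Chinese original, so silence is weaker evidence than usual. Birth weight and anomalies are also ordinary delivery-record items, and itemising safety outcomes is often left to an analysis plan. The second objection goes only so far: an analysis plan can choose and summarise variables, but it cannot create infant data or control-arm follow-up that the protocol does not schedule.

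**Conclusion.** The point holds in this form: the trial has no systematic infant safety comparison beyond liver function. Objective 5 promises information on harms to infants. Followed as written, the protocol would supply one organ system at two time points in up to 60 infants per arm, plus uncontrolled growth and IQ data in the TDF arm and whatever other events happen to be reported.

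This rests on three assumptions: that the English text reflects the procedures actually followed, that 'pregnancies' means the women, as elsewhere in the document, and that the infant liver tests apply to both arms, since no restriction is stated. If the Chinese original or the case-report form already collects birth and infant-illness data in both arms, the point reduces to naming them in the protocol.

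The primary outcome is not affected. This is a cheap improvement that lets the trial address its own objective.

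**What to change.** 1. In the safety monitoring text of Study Procedures, add that infant adverse events are asked about at each existing postpartum visit, in the same way in both arms.
2. Record from the delivery record, in both arms, gestational age, birth weight and length, and any congenital anomaly. Do this for every delivery, including those that meet the preterm exclusion in Study Design; otherwise a risk named by the protocol drops out of its own safety comparison. The Potential risk and Study Design statements on preterm delivery need to be reconciled.
3. List these items, with infant liver function, among the safety outcomes compared between arms in Statistical Analysis.

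The cost is a few extra case-report fields and some questions at visits that already take place. No new visit, sample or assay is needed. Growth and IQ to 2 years would remain a description of one arm and should be labelled so. Extending them to control infants would need follow-up beyond the last scheduled visit and is a separate, larger decision.
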